## Abstract

**Background:**

Acute retinal necrosis (ARN) is a rare but vision-threatening viral retinitis that can lead to severe visual impairment or blindness if not diagnosed and treated promptly. However, due to its rarity, there are limited large-scale data on the clinical characteristics, treatment approaches, and outcomes of ARN in Japan. A nationwide registry is needed to systematically collect data on ARN cases across Japan to improve understanding of this condition and optimize patient care. We have designed a national registry that collects data of patient characteristics, diagnosis, treatment, and visual outcome to generate evidence for the management of ARN.

**Methods and design:**

This research is a combined retrospective and prospective, multicenter cohort study of ARN in Japan from 1 April 2014–31 March 2029 (UMIN000056246). The registry has received Japan-wide approval from a national human research ethics committee. The following data will be collected: patient demographics, visual function at the initial visit and 6, 12, 24, and 36 months later, image data, diagnostic methods, virus analysis, indications and timing of vitrectomy, and complications. Customized software and platforms have been designed to permit data collection for a single baseline and multiple follow-up forms.

**Discussion:**

By analyzing the accumulated patient information, the results of this study will generate real-world evidence that will contribute to solve various important clinical issues in ARN. The results will be presented after data collection and analysis are completed.

## Introduction

Acute retinal necrosis (ARN) is a rare but severe infectious uveitis syndrome characterized by rapid necrosis of the retina, occlusive vasculopathy, and intense inflammatory responses within the eye. Delay in diagnosis and treatment can result in vision loss. This condition was first described in Japan in 1971 by Urayama et al. [1], and has since been recognized worldwide as a potentially sight-threatening ocular emergency. The causative agents of ARN are primarily members of the Herpesviridae family, including herpes simplex virus (HSV) types 1 and 2, and varicella-zoster virus (VZV). In Japan, real-time polymerase chain reaction (PCR) analysis of intraocular fluids is not covered by the universal health insurance system (public health insurance). However, identification of viral agents by performing PCR on intraocular fluid samples facilitates a definitive diagnosis of ARN [2–4]. Nevertheless, the diagnosis of ARN is primarily clinical, based on characteristic fundoscopic findings and supported by real-time PCR. A distinct feature of ARN is peripheral necrotic lesions that circumferentially progress to the posterior pole accompanied by occlusive vasculopathy, which is one of the diagnostic criteria of ARN [2]. The management of ARN poses several challenges, including difficulties in early diagnosis, variable responses to treatment, and a high rate of complications. The rapid progression of retinal necrosis and the potential of bilateral involvement necessitate prompt and aggressive intervention. However, the rarity of the condition and the lack of standardized treatment protocols complicate management. Moreover, the long-term prognosis remains guarded, with many patients experiencing recurrent episodes and permanent vision loss.

ARN is a relatively rare condition, with an annual incidence estimated at 0.63 cases per million population in the United Kingdom [5]. In Japan, ARN accounts for approximately 1.7% of all uveitis cases, underscoring its rarity but significant impact on those affected [6]. In Japan, where ARN has been recognized and studied extensively, the establishment of a nationwide registry represents a significant step toward improving patient care and advancing research in this challenging field. By consolidating data from multiple institutions, the registry will enable large-scale analyses that are not feasible in individual case reports or small case series. A report on the association between initial treatment regimen and retinal detachment rate and visual outcomes in patients with ARN in the American Academy of Ophthalmology IRIS^®^ Registry (Intelligent Research in Sight) has been published [7]. The insights gained from the nationwide registry in Japan will also be instrumental in addressing critical clinical questions, standardizing diagnostic and treatment protocols, and ultimately enhancing the quality of care for patients with ARN.

The primary objectives of the registry are to (1) characterize the clinical features, diagnostic approaches, virus type, and treatment patterns of ARN; (2) assess visual and anatomic outcomes in ARN patients treated with or without surgery; (3) identify visual prognostic factors associated with outcomes; and (4) compare the effectiveness of different treatment regimens. This information would provide valuable insights into ARN epidemiology, clinical features, treatment responses, and long-term outcomes. Such data are essential for developing evidence-based guidelines and optimizing management strategies. The registry would also facilitate collaborative research efforts facilitating the identification of prognostic factors and the evaluation of novel therapeutic approaches.

## Methods

### Study design and ethical considerations

The nationwide registry is named “Japan-acute retinal necrosis (J-ARN) registry”. The present research is a combined prospective and retrospective, multicenter, observational study of ARN in Japan from 1 April 2014–31 March 2029. The use of a combined retrospective and prospective design is due to the limited scope of the research that focuses on a rare and intractable disease with diverse treatment approaches. Recruiting a large number of participants is anticipated to be challenging.

During the prospective recruitment phase, participating sites will enroll consecutive patients as they visit for routine follow-up, to reduce the risk of selection bias, and Fig 1 outlines timepoints of enrolment, interventions, and outcomes. Recruitment commenced on 1 April 2025. For the retrospective component, medical records of the prospectively recruited patients will be reviewed retrospectively back to 1 April 2014, to accurately determine the index date of the initial diagnosis of ARN. This hybrid approach aims to maximize the use of available data while ensuring robust and unbiased participant inclusion, despite the challenges associated with studying a rare disease.

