**Fig 1 pone.0323822.g001:**
[figure not shown]
SPIRIT flow diagram for the schedule of enrolement, interventions, and assessments in our prospective study. Abbreviations: visual acuity (VA), herpes simplex virus (HSV), varicella zoster virus (VZV), proliferative vitreoretinopathy (PVR).

The Oita University Hospital Clinical Research Supervision Center, Biomedical Research Ethics Review Board approved the study protocol (No. 2810-D28) on 23 May 2024, and the study is registered in the University Hospital Medical Information Network Clinical Trials Registry (UMIN000056246). The Tokyo Medical University Hospital Research Ethics Committee approved the study protocol (No. E2024-0071) on 1 November 2024. The study will adhere to the principles of the Declaration of Helsinki and the Ethical Guidelines for Life Science and Medical Research Involving Human Patients.

For the prospective component of the study, written informed consent will be obtained from all recruited participants, including consent for the PCR assay. However, written informed consent from patients will not be required for retrospective review of clinical charts, as the study design does not involve randomization. Instead, an opt-out approach will be employed in accordance with the Ethical Guidelines for Medical and Biological Research Involving Human Subjects.

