### Sample size, inclusion and exclusion criteria

The goal of the study is to register a total of 500 eyes treated for ARN. The sample size was determined based on an estimation of number of eligible patients from a national uveitis survey in Japan [6]. Patients who meet the international diagnostic criteria for ARN and who have given written consent to participate in the prospective study, including intraocular fluid examination, will be eligible for registration [2,8]. Exclusion criteria are: (1) patient with retinal necrosis caused by pathogens other than HSV-1, HSV-2 or VZV, such as cytomegalovirus (CMV), (2) patient deemed unsuitable for the study by the investigator, and (3) patient in whom related diseases cannot be excluded despite meeting the inclusion criteria. In the case of exclusion from the study, clinical data until the date of consent acquisition will be registered, after which the study will be terminated.

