### Statistical analysis

The clinical profile as well as medical and surgical treatment options will be analyzed using descriptive statistics. Biostatisticians and information technology experts ([name] and [name]) will be involved in the planning, execution, and evaluation of the analyses. Multivariate analysis will be performed on changes in visual function over time and complications to identify influencing factors. Best-corrected visual acuity (BCVA) is converted to logarithm of the minimum angle of resolution (logMAR), and visual acuity worse than 0.01 is converted according to previous report [10] as follows: counting fingers, 2.6 logMAR; hand motions, 2.9 logMAR; light perception, 3.1 logMAR; no light perception, 3.4 logMAR. Data of continuous variables are expressed as mean and standard deviation or median and range, depending on normality of data distribution. Non-parametric data will be analyzed by Mann-Whitney U test or Kruskal-Wallis test, while parametric data will be analyzed by Student’s t-test or one-way ANOVA. Categorical variables will be expressed as total number and percentage, and the data will be analyzed by chi-squared test or Fisher’s exact test. The impact of clinical presentations, viral load, diagnostic methods, treatments, and complications will be estimated by odds ratios (ORs) with 95% confidence intervals (CIs). Survival analyses, especially Kaplan-Meier estimates, will be performed to evaluate visual prognosis, progression-free interval, and complications. Time-to-event data for 6, 12, 24, 36 month from the initial visit, the date of diagnosis, and/or vitrectomy were analyzed. A P value less than 0.05 will be considered statistically significant. Multivariate analyses (such as logistic regression analysis, cox proportional hazards regression, generalized estimating equations, and covariance structure analysis) will consider potential confounding variables related to treatment selection and outcomes.

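### Patients diagnosed before April 2025 enter only if they still attend follow-up and consent, so the plan's claim of unbiased inclusion is not supported

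*Protocol article*

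**What the plan says.** All references are to the protocol article.

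- *Study design and ethical considerations*, entry: "participating sites will enroll consecutive patients as they visit for routine follow-up, to reduce the risk of selection bias". Start date: "Recruitment commenced on 1 April 2025".
- Same section, source of the earlier data: "medical records of the prospectively recruited patients will be reviewed retrospectively back to 1 April 2014". The overall window is an "observational study of ARN in Japan from 1 April 2014–31 March 2029". The section presents the hybrid approach as "ensuring robust and unbiased participant inclusion".
- Same section, consent paragraph: "written informed consent from patients will not be required for retrospective review of clinical charts"; an opt-out approach is to be used instead.
- *Sample size, inclusion and exclusion criteria*: patients who meet the diagnostic criteria and "who have given written consent to participate in the prospective study, including intraocular fluid examination, will be eligible for registration". The target is 500 eyes.
- *Statistical analysis*: "Survival analyses, especially Kaplan-Meier estimates, will be performed to evaluate visual prognosis, progression-free interval, and complications". Time runs from the initial visit, the diagnosis and/or vitrectomy.
- *Discussion*, limitations: retrospective data are said to be more open to selection bias, which is linked to incomplete records. Voluntary participation by ophthalmologists is named separately. Selection on continued attendance is not mentioned.

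**The concern.** For a case diagnosed between 1 April 2014 and 31 March 2025, entry depends on something that happens after the clinical course has begun: the patient must still be coming to clinic after 1 April 2025 and must consent. This is a sample of prevalent cases. Whether an eye is still followed years later may well depend on retinal detachment (RD), proliferative vitreoretinopathy, silicone oil, recurrence or vision. These are the events and findings the registry records as outcomes.

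If it does, three of the four primary objectives are affected wherever pre-2025 cases contribute: visual and anatomic outcomes, prognostic factors, and comparison of treatment regimens. The distortion comes from who can enter, so a larger number of eyes gives a narrower interval around the wrong value. The text nevertheless presents the approach as securing unbiased inclusion, and a reader of the results would rely on that.

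**Working it through.** **1. Dates (from *Study design and ethical considerations*).**
- Whole window, 1 April 2014 to 31 March 2029: 15.0 years.
- Before recruitment: 11.0 years, and 11.0/15.0 = 73%. During recruitment: 4.0 years.
- A 36-month visit by 31 March 2029 needs a first visit by about 31 March 2026, which leaves 12.0 years of possible first visits. Of these, 11.0/12.0 = 92% precede recruitment.
- A case diagnosed before April 2022 must still be in care more than 36 months later to enter. Its 36-month outcome is therefore observed only given retention.

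**2. The plan's own figure.** The 500 eyes come from a national uveitis survey whose count is not given, so the figure cannot be reproduced. The point does not depend on it.

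**3. What selection on attendance could do.** The only input from the document is an RD risk of 47% during follow-up (*Discussion*), used as the true value. Assumptions: diagnoses are uniform over the 11 years before April 2025, and a case enters only if still attending on 1 April 2025.

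Share with RD among those entering = 0.47·A1 / (0.47·A1 + 0.53·A0), where A1 and A0 are the average probabilities of still attending with and without RD.

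(a) Constant yearly loss *l*: A = [1 − (1 − l)^11] / [−11·ln(1 − l)].

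| Yearly loss, RD / no RD | A1 | A0 | Share with RD |
|---|---|---|---|
| 20% / 25% | 0.372 | 0.303 | 52% |
| 15% / 30% | 0.466 | 0.250 | 62% |
| 10% / 40% | 0.592 | 0.177 | 75% |

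(b) Exponential attendance with mean *m* years: A = m·[1 − exp(−11/m)] / 11.

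| Mean years, RD / no RD | A1 | A0 | Share with RD |
|---|---|---|---|
| 6 / 4 | 0.458 | 0.340 | 54% |
| 6 / 2 | 0.458 | 0.181 | 69% |
| 4 / 4 | 0.340 | 0.340 | 47% |
| 4 / 6 | 0.340 | 0.458 | 40% |
| 2 / 6 | 0.181 | 0.458 | 26% |

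In the patterns under (b), only about 31-40% of pre-2025 cases would be captured.

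**4. Time-to-event estimates.** A simulation used the same 47% and exponential attendance, and further assumed a mean of 0.3 years to RD. The 3-year Kaplan-Meier RD risk counted from diagnosis was:

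| Mean attendance, RD / no RD | All counted from diagnosis | Risk time from enrolment, earlier events left out |
|---|---|---|
| 6 / 2 years | 71% | 50% |
| 4 / 4 years | 49% | 47% |
| 2 / 6 years | 29% | 47% |

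Delayed entry removes most of the distortion, but 87-94% of RD events in enrolled pre-2025 cases fell before enrolment and no longer count. Little information on early events is left.

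**5. How much the registry may lean on prevalent cases.** The *Introduction* gives 0.63 per million per year for the United Kingdom. Assuming that rate holds in Japan, with 120-125 million people and full capture:
- 0.63 × 120 = 75.6 and 0.63 × 125 = 78.75 patients a year; × 4 years = 302-315 patients.
- At an assumed 10-30% bilateral: 302.4 × 1.1 = 333 to 315 × 1.3 = 410 eyes, below 500.
- The rate needed for 500 eyes is 500/(4 × 125 × 1.3) = 0.77 to 500/(4 × 120 × 1.1) = 0.95 per million, that is 22-50% above the UK rate.

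**6. Consent text side by side.** The consent paragraph provides chart review without written consent. The design paragraph takes charts only from prospectively recruited patients, and the eligibility section requires written consent for registration. The passages do not say whose charts the opt-out covers.

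**The case against.** The strongest reply is that no bias has been demonstrated. The document gives no attendance, discharge or loss data, and if attendance is unrelated to outcome the RD share stays at 47%. That stands, and it rules out several stronger readings:

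- *RD will be overstated.* A reader might infer this from the 52-75% scenarios. They assume that RD patients stay longer; if blind eyes leave care sooner, the error runs the other way.
- *The whole registry is biased.* Cases first seen from 1 April 2025 are much less affected, and the descriptive objective also covers presenting features and virus type.
- *500 eyes cannot come from new cases.* The incidence is a UK figure, and the Japanese survey behind the target is not shown. A moderately higher Japanese rate would suffice, so only *probably* is warranted.
- *The Kaplan-Meier and Cox analyses ignore delayed entry.* The article names methods and time origins but does not define risk sets. A condensed article may leave that to an analysis plan, so the silence is not an error.
- *The opt-out has nobody to apply to.* It could cover pre-consent charts, or non-attenders under the full protocol. The text supports only that the passages need reconciling.

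It is also fair that the design paragraph words its claim as an aim, speaks of reducing the risk of selection bias, and that the limitations concede such bias. But that concession rests on other causes. None of this alters the entry rule, which this document fixes.

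**Conclusion.** The point holds in a limited form. As written, pre-2025 cases are selected on continued attendance and consent, and the claim of unbiased inclusion does not follow from the design. Outcome rates, prognostic associations and treatment comparisons from those cases are biased if attendance is related to outcome. That condition is plausible but not established, and the documents fix neither the sign nor the size of the bias.

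The range of about 26% to 75% around a true 47% shows what the mechanism could do. It rests wholly on assumed attendance patterns and is not a forecast. The exposure is broad, since 11 of the 15 study years precede recruitment and the target probably needs prevalent cases.

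**What to change.** 1. Make patients first seen on or after 1 April 2025 the main set for RD rates, time-to-event analyses and treatment comparisons. Report still-attending pre-2025 cases separately. If these enter a time-to-event analysis, start their risk time at enrolment and leave eyes that already had the event out of that event's risk set. Merely not counting the earlier events would keep those eyes in the denominator and push the estimate down.
2. Where the ethics approval covers it, use the opt-out route to list every ARN case diagnosed at each site since 1 April 2014, whether or not still attending, and add that complete list to the main set. Restrict the written-consent condition to prospective participants, so that the design, consent and eligibility texts agree. Later outcomes of discharged patients will still be missing and should be reported as such.
3. Replace the claim of unbiased inclusion with a statement that pre-2025 cases are selected on continued attendance, and add this to the limitations.

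Cost: under item 1 alone, a smaller main set and wider intervals. Item 2 needs an ethics clarification and chart abstraction of the registry items for each added case, which is more than one listing per site. Item 3 is a wording change.

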**Fig 1 pone.0323822.g001:**
[figure not shown]
SPIRIT flow diagram for the schedule of enrolement, interventions, and assessments in our prospective study. Abbreviations: visual acuity (VA), herpes simplex virus (HSV), varicella zoster virus (VZV), proliferative vitreoretinopathy (PVR).

The Oita University Hospital Clinical Research Supervision Center, Biomedical Research Ethics Review Board approved the study protocol (No. 2810-D28) on 23 May 2024, and the study is registered in the University Hospital Medical Information Network Clinical Trials Registry (UMIN000056246). The Tokyo Medical University Hospital Research Ethics Committee approved the study protocol (No. E2024-0071) on 1 November 2024. The study will adhere to the principles of the Declaration of Helsinki and the Ethical Guidelines for Life Science and Medical Research Involving Human Patients.

For the prospective component of the study, written informed consent will be obtained from all recruited participants, including consent for the PCR assay. However, written informed consent from patients will not be required for retrospective review of clinical charts, as the study design does not involve randomization. Instead, an opt-out approach will be employed in accordance with the Ethical Guidelines for Medical and Biological Research Involving Human Subjects.

### Sample size, inclusion and exclusion criteria

The goal of the study is to register a total of 500 eyes treated for ARN. The sample size was determined based on an estimation of number of eligible patients from a national uveitis survey in Japan [6]. Patients who meet the international diagnostic criteria for ARN and who have given written consent to participate in the prospective study, including intraocular fluid examination, will be eligible for registration [2,8]. Exclusion criteria are: (1) patient with retinal necrosis caused by pathogens other than HSV-1, HSV-2 or VZV, such as cytomegalovirus (CMV), (2) patient deemed unsuitable for the study by the investigator, and (3) patient in whom related diseases cannot be excluded despite meeting the inclusion criteria. In the case of exclusion from the study, clinical data until the date of consent acquisition will be registered, after which the study will be terminated.

### Diagnosis

Acute retinal necrosis is diagnosed based on the standard diagnostic criteria [2,8,9], including typical clinical presentation with peripheral necrotizing retinitis, and positive virologic tests using PCR analysis of intraocular fluids.

### Registered data

The following data will be collected (Table 1): height, weight, age, sex, laterality of ARN, medication history, history of shingles vaccination and herpetic diseases, drinking and smoking history, systemic disease, ocular disease, days from onset of ocular symptoms to first visit, subjective symptoms, best-corrected visual acuity, spherical equivalent, intraocular pressure, axial length, lens status, slit lamp finding (anterior chamber cells and flares, mutton-fat keratic precipitates), presence of vitreous opacity, fundus appearance (extent of yellowish white lesions), presence of retinal holes/tears, status of optic disc (swelling, redness, atrophy), status of the macula (edema, epiretinal membrane, necrosis), optical coherence tomography (OCT) data, treatment (antiviral agents, systemic corticosteroid, photocoagulation), date of surgery, surgical procedure, and complication.

**Table 1 pone.0323822.t001:** List of information collected for J-ARN registry.

Clinical data at initial visit	Treatment method, timing and adverse events	Events and viral copy number	Findings at 6, 12, 24, 36 months after initial visit
Height	Antiviral agents (intravitreal and/or intravenous and/or oral)	Maximum extension of yellow-white lesions	Best-corrected visual acuity
Weight	Systemic corticosteroids	Period until progression of yellow-white lesion stops	Slit lamp findings (AC cells, flare, mutton-fat KPs)
Age	Photocoagulation	Development of retinal detachment	Presence of retinal detachment
Sex	Surgery	Development of proliferative vitreoretinopathy	Presence of optic nerve atrophy
Race	Number of vitrectomy	Recurrence of ARN	Status of the macula (edema, epiretinal membrane, necrosis)
Systemic disease	Intraocular tamponade materials	Development of ARN in the contralateral eye	Presence of proliferative vitreoretinopathy
History of herpetic disease	Intraoperative and postoperative complications	Viral copy number measured during follow-up period	Presence of silicone oil
History of ocular disease			Complications
History of shingles vaccine			
Medication history			
Smoking history			
Days from onset of ocular symptoms to first visit			
Lesion laterality			
Subjective symptoms			
Best-corrected visual acuity			
Spherical equivalent			
Intraocular pressure			
Axial length			
Lens status			
Slit lamp findings (AC cells, flare, mutton-fat KPs)			
Presence of vitreous opacity			
Extent of yellow-white lesions			
Presence of retinal holes/tears			
Status of optic disc (swelling, redness, atrophy)			
Status of the macula (edema, epiretinal membrane, necrosis)			
Viral copy number of HSV-1, HSV-2 or VZV			

Abbreviations: AC, anterior chamber; ARN; acute retinal necrosis; KP, keratic precipitates; HSV, herpes simplex virus; VZV, varicella zoster virus

Decimal best-corrected visual acuity will be evaluated at the initial visit and at follow-up after 6, 12, 24, and 36 months. Decimal best-corrected visual acuity will be converted to logMAR units for statistical analysis. The collected data will be anonymized and registered online. The data center will be located within the hosting service of G-INGS Inc. (Fukuoka, Japan), ensuring maximum security for data storage and management. All data will be reviewed at least twice by the committee. The Committee will contact the participating institution for verification if any inconsistency or outlier is identified. If confirmation is not possible, the Committee will make the final decision.

A peripheral blood will be collected at the initial visit and thereafter as needed. Nonspecific inflammation tests such as erythrocyte sedimentation rate and blood count are sometimes included in the routine laboratory evaluation. The results of these tests are also essential for initiating therapy with anti-viral drugs and systemic corticosteroids.

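### No patient first seen after 31 March 2026 can reach month 36 within the study period, so 36-month results will rest mainly on previously diagnosed patients still in care, and pooling them with new cases blurs change over time.

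*Protocol article*

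**What the plan says.** All points are in the Methods of the Protocol article.

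- **Calendar** (Study design and ethical considerations): the registry is a "multicenter, observational study of ARN in Japan from 1 April 2014–31 March 2029", and "Recruitment commenced on 1 April 2025". No separate closing date for enrolment is given.
- **Schedule** (Registered data): "Decimal best-corrected visual acuity will be evaluated at the initial visit and at follow-up after 6, 12, 24, and 36 months". Table 1 gives the time origin in a column heading: "Findings at 6, 12, 24, 36 months after initial visit".
- **Entry** (Study design and ethical considerations): "participating sites will enroll consecutive patients as they visit for routine follow-up, to reduce the risk of selection bias". For the look-back, "medical records of the prospectively recruited patients will be reviewed retrospectively back to 1 April 2014". Eligibility (Sample size, inclusion and exclusion criteria) requires written consent to the prospective study.
- **Analysis** (Statistical analysis): multivariate analysis of change in visual function and of complications, Kaplan-Meier and Cox methods, generalized estimating equations, and "Time-to-event data for 6, 12, 24, 36 month from the initial visit, the date of diagnosis, and/or vitrectomy were analyzed". New and previously diagnosed patients are not distinguished there.
- **Limitations** (Discussion): retrospective data may be incomplete and more prone to selection bias. The shortened follow-up of new cases is not mentioned.

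**The concern.** The time from first recruitment to study end is 48 months, and the last scheduled visit falls 36 months after the initial visit. New cases can supply that visit only if first seen in the first of the four years. Patients diagnosed between April 2014 and March 2025 can also supply it, but by the stated entry route they join only if they are still attending once recruitment has opened.

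The two groups are selected differently. A prevalent patient is registered because he or she stayed in care; a new case is registered from the start of the disease. If their proportions differ between visits, a difference in mean acuity between month 6 and month 36 mixes change in the eyes with change in the set of patients. In a survival curve timed from the initial visit, a prevalent patient is also counted as at risk during a period in which he or she could not have been lost from the registry. Long-term visual outcome and prognostic factors are stated aims, so these results matter.

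**Working it through.** **1. Cut-off dates.** Inputs: study end 31 March 2029, visits at 6, 12, 24 and 36 months from the initial visit. Latest first visit = study end minus m months.

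| Visit | Latest first visit | Months of the 48 that qualify |
|---|---|---|
| 6 | 30 September 2028 | 42 |
| 12 | 31 March 2028 | 36 |
| 24 | 31 March 2027 | 24 |
| 36 | 31 March 2026 | 12 |

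Against those 12 months stand 132 months (April 2014 to March 2025) of earlier first visits. The article gives no expected number at any visit, so there is no figure of its own to reproduce.

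**2. Prevalent share at each visit.** Assumptions, none from the article: constant incidence, a constant yearly probability s of staying in care, equal capture of both groups, and new cases enrolled throughout the 48 months. Let a = m/12.

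- New cases able to supply visit m come from 4 − a years of first visits, each with weight s^a.
- Prevalent patients first seen less than a years before 1 April 2025 reach visit m after recruitment opened and also have weight s^a. Those first seen t > a years before must still be in care at t, with weight s^t, up to t = 11.

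Dividing by s^a, the ratio of prevalent to new cases is

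R = [a + I] / (4 − a), where I = (1 − s^(11−a)) / (−ln s), or 11 − a when s = 1,

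and the prevalent share is R/(R + 1).

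Month 36 (a = 3):
- s = 1.0: R = 3 + 8 = 11, share 11/12 = 92%
- s = 0.8: R = 3 + 3.73 = 6.73, share 87%
- s = 0.5: R = 3 + 1.44 = 4.44, share 82%
- s near 0: R approaches 3, share approaches 75%

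All visits:

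| s | Month 6 | Month 12 | Month 24 | Month 36 |
|---|---|---|---|---|
| 1.0 | 76% | 79% | 85% | 92% |
| 0.8 | 57% | 63% | 75% | 87% |
| 0.5 | 36% | 45% | 63% | 82% |

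**3. Lower capture of older cases.** If prevalent patients are captured c times as often as new ones, the share is cR/(cR + 1). At month 36:
- c = 0.5: 5.5/6.5 = 85% (s = 1.0), 77% (0.8), 69% (0.5)
- c = 0.25: 2.75/3.75 = 73% (s = 1.0), 63% (0.8), 53% (0.5)

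**4. How many had to stay in care beyond month 36.** Only patients first seen before April 2022 did. Their part of the month-36 set is I/(R + 1): 8/12 = 67% (s = 1.0), 3.73/7.73 = 48% (0.8), 1.44/5.44 = 26% (0.5).

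**5. If enrolment of new cases closed on 31 March 2026.** Every new case could reach month 36, and the denominator of R becomes 1 at every visit. At s = 1.0 the share is then 92% throughout. At s = 0.8, a + I is 4.55 at month 6 and 6.73 at month 36, so the share goes from 4.55/5.55 = 82% to 87%. The calendar cause of the shift is gone; a smaller shift from loss to follow-up remains.

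**The case against.** - **The article does not claim 36-month data for everyone.** A visit schedule is not a promise of completeness, and Kaplan-Meier and Cox methods censor at study end by construction. That stands: a reader might infer that the plan treats month 36 as available for the whole cohort, but no sentence says so. Ordinary censoring, however, does not deal with late entry of prevalent patients or with the changing mix in visit-by-visit acuity.
- **The hybrid design is deliberate and its bias is conceded.** Rarity is given as the reason, and the limitations mention selection bias. The concession is general and covers neither the cut-off nor pooling across visits.
- **A condensed article leaves expected numbers and reporting strata to the full documents.** Fair, and their absence is not the point. The point is what the printed dates, entry route and time origin imply together.
- **Enrolment might close early.** No closing date is given. Closing on 31 March 2026 would let every new case reach month 36, so step 2's shares across visits are conditional on continued enrolment.
- **Patients no longer attending might enter through the opt-out route for chart review.** This is possible, but it sits uneasily with the look-back being confined to recruited patients and with the written-consent condition.

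Two stronger readings are tempting. One is that month 36 will come almost entirely from survivors. The share nears 92% only when nearly everyone stays in care, and then there is little survivor selection; patients first seen from April 2022 to March 2025 need stay no longer than a new case. The other is that months 6 and 12 are dominated by new cases. At retention of 0.8 or above they are 57–79% prevalent.

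**Conclusion.** The cut-off is exact, given that 31 March 2029 ends data collection: no patient first seen after 31 March 2026 can contribute month-36 data. The Statistical analysis section also allows diagnosis or vitrectomy as origin; the same date then applies to that event.

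Month-36 results will rest mainly on patients diagnosed before recruitment opened who were still attending: about 82–92% under constant incidence, equal capture and retention of 0.5–1.0, and about 53–85% with capture a quarter to half as high. These ranges are modelled; the article supplies neither retention nor capture. If enrolment runs past March 2026, the prevalent share rises with each visit at every retention level tried, so pooled trends partly reflect composition. A headcount of new cases at month 36 cannot be derived from the article without assuming a capture rate.

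This does not make the registry unfit for long-term outcomes. It means that the pooled 36-month results need to be separated by how patients entered.

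**What to change.** 1. Either state that enrolment of new cases closes on 31 March 2026, or state the first-visit cut-offs from step 1 and treat visits due after 31 March 2029 as administratively censored, not missing.
2. Define incident patients as first seen on or after 1 April 2025 and prevalent patients as first seen earlier. Report every time point and time-to-event curve separately for the two. Step 5 shows that this is needed even if enrolment closes early.
3. In Kaplan-Meier and Cox analyses, let prevalent patients enter the risk set at their enrolment date (delayed entry).
4. Describe change over time only within eyes seen at both visits, or from a mixed model.
5. Qualify the statement in Study design and ethical considerations that the hybrid approach makes inclusion robust and free of bias.

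Cost: wording and analysis of data already collected. Intervals for incident patients at month 36 will be wider. Under delayed entry, events that prevalent patients had before enrolment no longer count in the curves and would be described separately. Closing new enrolment early would also reduce the number of new cases at the earlier visits. The article names no main time point, so none has to change.
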